**Fig. 1 Fig1:**
[figure not shown]
Flow of the study

### Outcome measures

#### Measurement of fibular positional fault from radiograph

A weight-bearing (neutral ankle in standing position) X-ray (55 k Vp and 2.1 mAs) will be taken of the affected ankle of the participant. The participant will be asked to stand on the foot to be imaged on a wooden box with the knee slightly flexed to simulate mid-stance of the gait cycle, with the foot of the non-stance leg hanging in a relaxed manner. The imaged leg will be maintained ~ 2 cm away and parallel to the image receptor. The same instructions will be given to all participants and the participant’s leg position will be monitored throughout the procedure. If any leg rotation is noted on imaging, the X-ray will be redone. The central ray will be centred at the base of the metatarsals and perpendicular to the image receptor, and the focal-film distance will be set to 110 cm. The participant will be allowed to hold on to body of the X-ray machine for balance if required.

Radiographic images will be digitally obtained using Merge PACS™ software (Merge Health Care, 2012). The fibular position will be measured as the distance between the anterior edge of the distal fibula and the anterior edge of the distal tibia [27] (Fig. 2). The test-retest reliability intra-class correlation coefficient (ICC)_3,1_ has been estimated as 0.98, with a SEM of 0.64 mm for this measurement, and for intra-tester reliability, the ICC_3,1_ is 0.92 and SEM is 0.72 mm [27].

**Fig. 2 Fig2:**
[figure not shown]
Fibular position measurement; the distance between the anterior edge of the distal fibula and the anterior edge of the distal tibia (right ankle, 4.2 mm in this image)

#### Weight-bearing dorsiflexion range of movement

Weight-bearing DFROM will be measured using the weight-bearing lunge test. The participant will be instructed to lunge towards the wall, touch their knee to the wall, and keep their heel in contact with the floor. Then the participant will be asked to move their foot away from the wall in 1 cm increments until the heel no longer maintains contact with the floor or the knee is no longer in contact with the wall. Maximal dorsiflexion will be considered to be the greatest distance between the great toe and wall with the participant’s knee maintaining contact with the wall [18, 40]. Both inter-rater reliability (ICC = 0.80–0.99) and intra-rater reliability (ICC = 0.65–0.99) have been reported as high for this test [41]. The same procedure will be followed for the opposite leg. Each centimetre away from the wall in the lunge test represents approximately 3.6 degrees of dorsiflexion [42]. Three test attempts will be performed and the average value will be used for analysis.

#### Pressure pain threshold

PPT measurements will be obtained in each leg from two local points (to assess local hypersensitivity) and one remote body area (to assess central sensitisation), in accordance with the method used in a previous study on acute ankle sprain [24]. The points include anterior to the lateral malleolus over the anterior talo-fibular ligament, inferior to the medial malleolus over the deltoid ligament, and over the proximal third of the tibialis anterior muscle belly.

A Freedom Tracker hand-held algometer (JTECH Medical, Salt Lake City, UT, USA) will be used for measuring PPT. A probe (contact surface of 1 cm^2^) will be placed perpendicular to the skin and pressure will be applied (40 kPa/s). The participant will be asked to indicate when the feeling of the stimulus changes from ‘pressure only’ to ‘discomfort’ by pressing an indicator switch [43, 44]. This process will be performed three consecutive times and a 10 s rest period will be allowed between each set of measurements. Pressure algometry is considered a stable and reliable measure of PPT [45]. The inter-rater reliability of pressure algometry has been reported to be high when the algometer pressure is applied at a consistent rate (ICC 0.91, 95% CI 0.82–0.97) [46].

#### Pain intensity

Current pain intensity will be assessed using the visual analogue scale (VAS) which consists of a 100 mm horizontal line, with ‘no pain’ anchored on the left of the line and ‘worst possible pain’ anchored on the right. The validity of the VAS for detecting changes in pain intensity has been supported by several studies [47, 48].

The participant will also be asked to indicate all areas in which they currently feel symptoms on a body chart. The areas in which they feel ‘pain’ will be shaded; the areas in which they feel ‘tingling, pricking, or burning’ will be circled; and the areas where they feel ‘numbness, heaviness or other sensations’ will be indicated on the chart by an ‘N’.

#### Function

Self-reported physical function of the participant will be evaluated using the FAAM which consists of a 21-item ADL subscale and an 8-item sport subscale [34]. This tool has been documented as a reliable, responsive and valid measure of physical function for individuals with a broad range of musculoskeletal disorders of the lower leg, foot and ankle [34]. The Foot and Ankle Outcome Score (FAOS) questionnaire comprising 42 items will also be used, and has been reported as also being a reliable and valid measure (ICCs reported as 0.78, 0.86, 0.70, 0.85, 0.92 for the five subscales of pain, symptoms, ADL, sport and recreation function, and foot- and ankle-related quality of life, respectively) [49].

Further, the participant will be asked to identify up to three important activities that they are unable to perform or are having moderate to extreme difficulty performing due to pain. For each activity, the participant will be asked to rate between 0 and 10 the level of difficulty they experience performing that activity using the Patient-Specific Functional Scale (PSFS) [35]. The construct validity of the PSFS is well supported, and the test-retest reliability has been assessed as moderate to good (ICC2,1 = 0.713) [36].

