## Background

Up to 40% of patients with an initial ankle sprain develop chronic ankle instability (CAI), which is frequently associated with recurrent sprains and persistent pain [1, 2]. A recurrent subjective perception of the ankle joint ‘giving way’ is clinically indicative of CAI [3], which is defined as “repetitive bouts of lateral ankle instability resulting in numerous ankle sprains” [4]. Clinical management of CAI often involves balance and sport-related activity training [5]. In a recent meta-analysis, preliminary evidence was also found supporting joint mobilisation as a clinically effective intervention in improving dynamic balance and dorsiflexion range of motion in CAI [6].

Several ankle joint mobilisation procedures have been developed and described by renowned manual therapists such as Geoffrey Maitland, Freddy Kaltenborn and Brian Mulligan, and are commonly used in rehabilitation [7]. These procedures are applied to a joint, either in the form of non-thrust passive joint mobilisations, high velocity thrust manipulation, or Mobilisation With Movement (MWM). MWM is defined as the application of a sustained passive accessory movement to a joint while the patient actively performs a task/movement that was previously identified as being painful or limited [8]. After manual application of MWM, tape is applied to help maintain the glide and corrected fibular position [9]. Biomechanically and neurophysiologically mediated mechanisms have been proposed to explain how these joint mobilisation procedures may work [8, 10]. The proposed neurophysiological mechanisms are based on animal [11] and human experiments [12] related to pain science and motor systems [8]. These have shown that joint manual therapy techniques including MWM, activate a descending pain inhibitory pathway which is non-opioid mediated [8]. One proposed biomechanical mechanism relates to a reduction of an entrapped meniscoid or synovial fringe by a specifically directed MWM glide particularly in those instances where only one repetition is required to bring about a substantial and long lasting effect [8].

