Of our recent systematic review and meta-analysis identified greater effects for MWM and Mulligan taping compared to Maitland joint mobilisation (with and without traction) and joint thrust manipulation [6, 13]. Dorsiflexion range of motion and self-reported instability were some of the outcomes for which there was evidence of improvement from MWM, although the long term benefits were unclear [14–16]. Most of the previous studies on chronic ankle sprains have applied MWM to the talocrural joint [14–18], and few studies have applied MWM taping [19–21]. However Mulligan proposes that an anterior fibular positional fault commonly results from ankle inversion sprains, and that a MWM using a posterior glide of the fibula to correct this should be trialled after 48 h following such an injury [22]. Patients with recurrent ankle sprains may also benefit from this MWM treatment combined with taping aimed at maintaining the posterior fibula glide, with reportedly less ‘giving way’ and greater confidence in using the ankle in patients with functional instability and pain [22]. Therefore this study is designed to evaluate the clinical benefits of the fibular posterior glide MWM with Mulligan taping, and whether it corrects any demonstrable positional fault which may exist. The prevalence of pain in people with CAI is high (60.1%) [23] and to our knowledge no studies have assessed the effect of MWM on pain. In addition, the present study will assess the effects of MWM on pressure pain threshold in CAI. The presence of localized peripheral sensitization has been previously identified in acute inversion ankle sprains [24] and in subacute ankle sprains [25]. Balance impairments in CAI are frequently reported in the literature and MWM has been found to be effective immediately after application, but there is presently insufficient research to determine the short term benefits of MWM for balance impairments [6]. The present study plans to address this deficiency in the literature as well.

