### Participants

Participants aged 18 years or over will be recruited from the general community in the Newcastle area of New South Wales, Australia through flyers posted on noticeboards in shopping centres, the University of Newcastle main campus, and various other public places. Recruitment advertising will also be via University of Newcastle social media channels. Volunteers with CAI will be accepted into the study if they satisfy the inclusion and exclusion criteria as endorsed by the International Ankle Consortium [29], except the time period for experiencing at least two episodes of giving way is changed from 6 months to 12 months to account for the seasonal nature of some sports (Table 1).

**Table 1 Tab1:** Inclusion and exclusion criteria

Inclusion criteria	Exclusion criteria
• A history of at least one significant ankle sprain; - Initial sprain must have occurred at least 12 months prior to study enrolment - Was associated with inflammatory symptoms - Created at least one interrupted day of desired physical activity - The most recent injury must have occurred more than 3 months prior to study enrolment	• A history of previous surgeries to the musculoskeletal structures (i.e., bones, joint structures, nerves) in either lower extremity • A history of a fracture in either lower extremity requiring realignment • Acute injury to musculoskeletal structures of other joints of the lower extremity in the previous 3 months that impacted joint integrity and function (i.e., sprains, fractures), resulting in at least one interrupted day of desired physical activity • Have conditions for which manual therapy is generally contraindicated (such as the presence of a tumour, fracture, rheumatoid arthritis, osteoporosis, prolonged history of steroid use, or severe vascular disease)
• A history of the previously injured ankle joint ‘giving way’ and/or recurrent sprain and/or ‘feelings of instability’ - Participants should report at least two episodes of giving way in the 12 months prior to study enrolment	• Have conditions for which radiological imaging is contraindicated (e.g., pregnancy)
• Self-reported ankle instability should be confirmed with the Cumberland Ankle Instability Tool (CAIT) (≤24)	• Have conditions for which taping is contraindicated (e.g., allergy to strapping tape)

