• General self-reported foot and ankle function questionnaire minimum score (Foot and Ankle Ability Measure (FAAM): activities of daily living (ADL) subscale < 90%, sport subscale < 80%)	• Receiving concurrent treatment - The most recent treatment for the ankle condition should have been received at least a week prior to study enrolment
	• Inability to read English

Data collection will be carried out at the physiotherapy and radiography research laboratories of the School of Health Sciences, The University of Newcastle, Australia.

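### The Patient-Specific Functional Scale prompt is tied to pain in a trial that recruits on instability, so this non-primary score may be missing or unrepresentative for pain-free participants (minor)

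*Protocol article*

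**What the plan says.** The Function section of the protocol article lists three self-report instruments.

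- **FAAM:** "Self-reported physical function of the participant will be evaluated using the FAAM which consists of a 21-item ADL subscale and an 8-item sport subscale". Its description contains no pain restriction. Sample size and data analysis names its two subscales as the primary outcome.
- **FAOS:** 42 items, with "five subscales of pain, symptoms, ADL, sport and recreation function, and foot- and ankle-related quality of life". Pain is one subscale of five.
- **PSFS:** the participant is asked to "identify up to three important activities that they are unable to perform or are having moderate to extreme difficulty performing due to pain", and rates the difficulty of each from 0 to 10.

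Only the PSFS is worded around pain; the limiting words are "having moderate to extreme difficulty performing due to pain". Table 1 (Participants) sets no pain criterion. Its symptom requirement is "A history of the previously injured ankle joint ‘giving way’ and/or recurrent sprain and/or ‘feelings of instability", with at least two episodes of giving way in the past 12 months. It adds a Cumberland Ankle Instability Tool (CAIT) score of 24 or less and FAAM limits: "activities of daily living (ADL) subscale < 90%, sport subscale < 80" per cent. The Background says that a recurrent sense of giving way "is clinically indicative of CAI", and on pain it states: "The prevalence of pain in people with CAI is high (60.1" per cent).

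**The concern.** The prompt and the population do not match. Every participant must enter with reduced function, so each should have activities worth naming. The pain qualifier can rule those activities out for someone whose limitation comes from giving way or lack of confidence in the ankle. The Background's own figure implies that a sizeable minority of people with this condition have no pain.

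Two things are at stake, both confined to the PSFS.

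1. **Completeness.** A participant with no eligible activity has no baseline score. The planned last-observation-carried-forward rule cannot help, because there is nothing to carry, so an intention-to-treat analysis of all participants cannot be achieved on this scale.
2. **Meaning.** Among those who do answer, the score leans towards how far pain interferes with activity. The Discussion plans to relate fibular position to pain and to function as separate outcomes, and a function score elicited through pain blurs that separation.

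Activities that were never elicited cannot be recovered at the analysis stage, so the wording is worth settling before data collection.

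**Working it through.** **Step 1. Is the sample size affected?**
Inputs from Sample size and data analysis: FAAM ADL difference 8.0, SD 5.68; FAAM sport difference 9.0, SD 7.42; power 0.80; alpha 0.05 (taken as two-sided); 30% drop-out; 16 per group.

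Formula: n per group = 2 × (1.960 + 0.842)² × (SD/difference)², then divided by (1 − 0.30).

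- Sport: 2 × 7.85 × (7.42/9.0)² = 10.7, rounded up to 11; 11/0.70 = 15.7, rounded up to **16**.
- ADL: 2 × 7.85 × (5.68/8.0)² = 7.9, rounded up to 8; 8/0.70 = 11.4, rounded up to 12.

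The stated 16 per group is reproduced from the FAAM sport inputs. The PSFS does not enter the calculation, so its wording cannot alter it.

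**Step 2. How many participants might have no eligible activity?**
Input: 60.1% with pain (Background), a figure for people with chronic ankle instability in a cited source. Applying it to this sample, and treating every pain-free person as having nothing to name, are assumptions.

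- Share without pain: 1 − 0.601 = 0.399.
- Expected number: 0.399 × 32 = 12.8, about **13 of 32**, or 0.399 × 16 = 6.4 per group.
- 95% binomial range for 32 participants: 7 to 18.

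**Step 3. What would that do to precision on the PSFS?**
With an unchanged SD and a share *s* unscored, the standard error of the group difference is multiplied by 1/√(1 − s). The true *s* is unknown, so a range is shown.

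| Share unscored (assumed) | Number of 32 | Standard error multiplied by |
|---|---|---|
| 10% | 3.2 | 1/√0.900 = 1.05 |
| 20% | 6.4 | 1/√0.800 = 1.12 |
| 39.9% (cited prevalence) | 12.8 | 1/√0.601 = 1.29 |
| 50% | 16.0 | 1/√0.500 = 1.41 |

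At the cited prevalence, the standardised difference detectable with 80% power (two-sided t-test, alpha 0.05) changes as follows.

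- Before drop-out: 16 per group falls to 16 × 0.601 = 9.6, and the detectable difference rises from 1.02 to 1.35.
- After 30% drop-out: 11.2 per group falls to 11.2 × 0.601 = 6.7, and it rises from 1.24 to 1.67.

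The article claims no power for the PSFS. These figures show what information could be lost and do not indicate a broken power statement.

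**The case against.** The case on the other side is substantial, and most of it limits the point.

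- **A reader might infer that the trial fails to measure limitation caused by instability.** The article does not support this. A pain-free participant limited by giving way still has a FAAM score, which is the primary outcome, as well as the FAOS symptom, daily-living, sport and quality-of-life subscales. Static and dynamic balance are measured, global perceived effect asks about ankle complaints in general, and new ankle injuries are logged by telephone. The gap lies in the PSFS alone.
- **A reader might also take it as fact that some 40% of participants will have no valid score.** That is not established. The cited source's definition of pain is not given, and its population was not selected by this trial's FAAM limits. Having any pain is also different from having an activity limited by pain, so the true share could lie on either side of 40%.
- **The sentence is ambiguous.** The pain qualifier may govern only the difficulty limb, leaving activities the participant cannot do at all unrestricted. On that reading fewer people are left with nothing to name. Activities that are difficult because of instability are still excluded, and the ambiguity itself is a reason to reword.
- **Pain is a legitimate target.** Pain intensity is among the stated aims, and the Background says that, to the authors' knowledge, no study has assessed the effect of the technique on pain. A pain-anchored item is therefore not plainly out of place. The article nevertheless files the PSFS under function, and pain has its own measures.
- **No tilt between arms is shown.** On the natural reading that activities are named at baseline, before treatment, the loss is one of precision and representativeness, with no bias between groups.

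What remains is a real mismatch between one stated prompt and the stated entry criteria.

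**Conclusion.** The point holds as a minor one. The PSFS prompt asks for activities made difficult by pain in a trial that recruits on instability and low function. Scores may therefore be missing, or may describe the wrong limitation, for participants without pain. The size is about 13 of 32 participants, with a standard error about 29% larger on this scale. Both figures rest on three assumptions: that the cited 60.1% applies to this sample, that every pain-free participant has no eligible activity, and that the SD is unchanged among those scored. If fewer are affected the loss shrinks, to about 5% on the standard error when 10% are unscored. The FAAM primary outcome, the 16 per group and the remaining function and balance measures are unaffected.

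**What to change.** In the Function section and on the PSFS form, replace *due to pain* with *because of their ankle problem (for example pain, giving way or instability)*, worded so that the qualifier clearly covers both the activities the participant cannot do and those that are difficult.

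The cost is one phrase, with no additional visit, staff time or analysis. The one small loss is that the PSFS will no longer be a pain-specific function item. Pain remains covered by the 100 mm visual analogue scale and the FAOS pain subscale.

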#### Static balance

For static balance, the participant will stand barefoot on the centre of a force plate (KISTLER 9260AA6, Winterthur, Switzerland), assuming a standardized single leg stance position. The participant will then be instructed to flex the other leg slightly at the hip, with the knee flexed to 90 degrees. Their arms will be crossed at their chest with each hand resting on the opposite shoulder. Measurements will be recorded with both ‘eyes open’ and ‘eyes closed’. For ‘eyes open’, the participant will be asked to maintain a fixed gaze on a cross marked on the wall three metres in front of them and remain as still as possible for 10 s [50]. For ‘eyes closed’, the participant will be asked to close their eyes and remain as still as possible for 10 s [50]. If the participant is unable to stand for 10 s, the standing time achieved will be recorded. Only averaged Centre of Pressure (CoP) data including sway velocity, sway area per second, sway average amplitude and sway maximal amplitude will be used in the analysis to maintain consistency. CoP data obtained through the force platform will be acquired at 100 Hz [21].

#### Dynamic balance

Dynamic balance will be assessed using the Star Excursion Balance Test (SEBT) which has been shown to be a reliable measure to identify dynamic balance deficits in patients with a variety of lower extremity conditions [51]. The participant will be asked to establish a stable base of support on the stance limb in the middle of the testing grid on a force plate (KISTLER 9260AA6, Winterthur, Switzerland). While standing on a single limb, the participant will be asked to reach as far as possible with the reaching limb along each line (anterior, postero-medial and postero-lateral directions), lightly touching the line with the most distal portion of the reaching foot without shifting weight or coming to rest on the foot of the reaching limb. The participant will then be asked to return the reaching limb to the starting position in the centre of the grid. If the individual lifts or shifts any part of the foot of the stance limb during the trial, the trial will be not considered as complete [51].

After performing a maximum of four non-recorded trials for familiarisation, the next trial for each direction will be recorded for the purpose of analysis [52, 53]. Normalised SEBT values will be obtained by dividing the excursion distance by the participant’s leg length (the distance between the anterior superior iliac spine and the ipsilateral medial malleolus), and then multiplying by 100 [52, 54]. Data for centre of pressure (CoP) velocity (V) to quantify spatio-temporal parameters (VCoP-total, VCoP-mediolateral, VCoP-anteroposterior) will be acquired at 100 Hz, under the foot during unipodal stance [52].

